## Methods/design

### Study design

This is a prospective, single-center, randomized, double-blind controlled study. We will enroll 78 stable CHD patients who have a 50 to 70% stenosis in major coronary arteries and whose FFR > 0.80 and IMR > 25. They will be randomly divided into the salvianolate group or the placebo group. The former group will be given intravenous salvianolate (200 mg salvianolate dissolved in 100 ml 0.9% sodium chloride injection, intravenous drip for 30 min) after the first measurement of IMR. The latter group will be intravenously given matching 0.9% normal saline 100 ml. Thirty minutes later, both groups will undergo reevaluation of IMR. For the subsequent 7 days, the salvianolate group will be intravenously infused with salvianolate 200 mg/day and the placebo group will continue to use matching 0.9% normal saline per day. Other medications will be used according to clinical needs. After 7 days, all patients will be assessed by the Seattle angina scale, quality of life scale, Holter electrocardiography, and 6-min walk test.

The trial protocol has been approved by the Institutional Ethics Committee of Sir Run Run Shaw Hospital of Zhejiang University and has been registered in the Chinese Clinical Trial Registry (ChiCTR1800018772). All patients will provide written informed consents before randomization.

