### Inclusion and exclusion criteria

Seventy-eight stable CHD patients with 50 to 70% stenosis in major coronary arteries, FFR > 0.80, and IMR > 25 at Sir Run Run Shaw Hospital of Zhejiang University will be enrolled in this trial. Detailed inclusion and exclusion criteria are shown in Table 1. The attending physician of the patient is responsible for inclusion and exclusion assessment.

**Table 1 Tab1:** Inclusion and exclusion criteria

Inclusion criteria	Exclusion criteria
• Angina pectoris • CAG showed 50 to 70% stenosis in major coronary arteries; FFR > 0.8, IMR > 25; • Patients received no salvianolate treatment previously.	• Patients with left main disease; • Patients with severe cardiac insufficiency (New York Heart Association grade III or higher), severe renal insufficiency (eGFR < 60 ml/min), liver dysfunction (ALT > 3 × URL), and asthma history; • Severe cerebrovascular disease; infection, hematopoietic dysfunction, tumor or mental illness; • Combined malignant arrhythmia or third degree atrioventricular block; • Currently taking other Chinese herbs for the treatment of angina; • Pregnant or breastfeeding women; • Currently participating in other clinical trials; • Allergic to known ingredients of salvianolate; and • The investigator considers it unsuitable for inclusion in other circumstances, or the patient or family members do not agree with the study’s treatment plan.

*CAG*, coronary angiography; *FFR*, fractional flow reserve; *IMR*, index of microcirculatory resistance; *eGFR*, estimated glomerulus filtration rate; *ALT*, alanine aminotransferase; *URL*, normal reference level

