**End points**			
Seattle angina scale	X		X
Quality of life scale	X		X
Holter electrocardiography	X		X
6-min walk test	X		X
IMR	X	X	

*CBC*, complete blood count; *Scr*, serum creatinine; *BUN*, blood urea nitrogen; *UA*, uric acid; *K*, potassium; *Na*, sodium; *Cl*, chloride; *ALT*, alanine aminotransferase; *AST*, aspartate aminotransferase; *BIL*, bilirubin; *cTnT/cTnI*, cardiac troponin T/I; *IMR*, index of microcirculatory resistance

In the screening stage, the investigator conducts a baseline assessment and gets the informed consent and randomization. Coronary angiography, FFR, and IMR will be used to determine whether the inclusion and exclusion criteria are met, and then informed consent should be signed by the patient or the authorized person. The web-based randomization assigned those eligible patients 1:1 ratio to either the salvianolate or the placebo group. The secretary of the catheterization room accesses the website via account password and is responsible for randomization. Block randomization stratified by sex will be implemented and it is blind to those who enroll participants or assign interventions. In the immediate phase, the patients will receive an IMR test again after 30 min of intravenous infusion and the research nurses will record the IMR value. In the in-hospital follow-up period, complete blood count (CBC), serum electrolytes (potassium (K), sodium (Na), chloride (Cl)), liver function (alanine aminotransferase (ALT), aspartate aminotransferase (AST), bilirubin (BIL)), renal function (serum creatinine (Scr), blood urea nitrogen (BUN), uric acid (UA)), fasting glucose, lipid profile, cardiac troponin T/I (cTnT/cTnI), echocardiography, Seattle angina scale, quality of life scale, Holter electrocardiography, and 6-min walk test will be collected after continuous intravenous salvianolate 200 mg/day for 7 days.

All serious adverse events must be reported to the sponsor immediately or within 24 h in CRFs. The attending physicians are responsible for data entry. The data monitoring committee is responsible for data security and accuracy. Committee members ([name], [name], [name], and [name]) have access to the final dataset and periodically range check for data values.

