### End points

The primary end point will be the IMR change in the immediate phase during the coronary angiography procedure, and the secondary end points will be the total ischemic burden assessed by the Seattle angina scale, quality of life scale, Holter electrocardiography, and 6-min walk test after 7 days before discharge. The safety end point will be the abnormal blood tests and self-reported adverse events.

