### Analysis

All data will be presented as percentages, mean ± standard deviation (SD), or median (quartile range). As the population variance *σ*^2^ is unknown, the confidence interval of the population mean *μ* is calculated by the formula $$ \overline{X}\pm \frac{S}{\sqrt{n}}{t}_{\alpha}\left(n-1\right) $$. Symbol $$ \overline{X} $$, *s*, and *n* are the sample mean, SD, and sample size, respectively, while *α* represents the significant level. The confidence interval of the difference between means will also be calculated by $$ \overline{X}\pm {S}_{{\overline{X}}_1-{\overline{X}}_2}{t}_{\raisebox{1ex}{$\alpha $}\!\left/ \!\raisebox{-1ex}{$2$}\right.}\left({n}_1+{n}_2-2\right) $$, in which $$ {S}_{{\overline{X}}_1-{\overline{X}}_2} $$ is the standard error of the difference of means. The adjusted Wald confidence intervals are used to estimate confidence intervals for proportions and the difference between the two population proportions [17].

IMR changes between the two groups will be compared by independent *t*-test or Mann-Whitney *U* test, while IMR changes before and after the use of salvianolate in the same group will be compared by paired *t*-test or Wilcoxon test. Analysis of covariance will be used if the baseline and follow-up IMRs are not highly correlated (*r* ≤ 0.8) [18, 19]. If the variables are not normally distributed, they will be transformed into normal distribution by logarithm. Different hypothesis testing, including *t*-test or nonparametric tests for continuous variables as well as *χ*^2^ test for categorical variables, will be used for the secondary end points assessed by the Seattle angina scale, quality of life scale, Holter electrocardiography, and 6-min walk test. The safety end point in our trial will be the abnormal blood tests including the abnormal liver function and self-reported adverse events such as dizziness and headache. The rate of abnormal liver function and other adverse events between the salvianolate group and the placebo group will be compared by *χ*^2^ test.

In our trial, stable CHD patients with myocardial microcirculatory disturbances form the population of interest, and participants with 50 to 70% stenosis in major coronary arteries, FFR > 0.80, and IMR > 25 form a sample. The end point of interest will be the IMR change in the immediate phase and the total ischemic burden assessed by the Seattle angina scale, quality of life scale, Holter electrocardiography, and 6-min walk test in the follow-up period.

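### The planned within-group paired test of IMR uses the eligibility reading (IMR > 25) as its 'before' value, so regression to the mean can yield a significant fall without a drug effect

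*Protocol article*

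**What the plan says.** Eligibility (Table 1) requires "CAG showed 50 to 70% stenosis in major coronary arteries; FFR > 0.8, IMR > 25". Under Implementation and study procedures, "Coronary angiography, FFR, and IMR will be used to determine whether the inclusion and exclusion criteria are met". Under Study design, the infusion follows directly "after the first measurement of IMR", and then "Thirty minutes later, both groups will undergo reevaluation of IMR". Table 2 lists IMR at screening and in the immediate phase and nowhere else. No separate baseline is taken after selection, so the reading that admits the patient is also the starting value for the change.

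The End points section reads: "The primary end point will be the IMR change in the immediate phase during the coronary angiography procedure". For this end point the Analysis section plans two kinds of test:

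- **Between the arms:** "IMR changes between the two groups will be compared by independent" t-test or Mann-Whitney U test. In addition, "Analysis of covariance will be used if the baseline and follow-up IMRs are not highly correlated", with r ≤ 0.8 as the cut-off.
- **Within an arm:** "IMR changes before and after the use of salvianolate in the same group will be compared by paired" t-test or Wilcoxon test.

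The Analysis section sets P < 0.05 as the criterion for significance. It does not exempt the within-group test or label it descriptive.

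**The concern.** The paired test's null hypothesis is zero mean change. In patients admitted because one reading was above a threshold, that null is generally false even for an inert infusion. Some of them exceeded 25 partly through measurement noise or momentary variation, and that part does not recur at the second reading. Any effect of time, of the saline volume or of repeating the measurement is also mixed into the change. A small P-value therefore cannot be read as an effect of salvianolate.

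The placebo arm removes these components because they are expected equally in both arms, and a test within one arm discards that protection. At stake is interpretation: the article would hold a second P-value on the primary variable, judged at the same threshold, which can be significant when the randomised comparison is not.

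**Working it through.** **Inputs from the article.** Selection at IMR > 25 (Table 1); two readings, the first being the selecting one (Study design, Table 2); about 36 patients per group before allowance for loss (Sample size); criterion P < 0.05 (Analysis). The article gives no error rate for the paired test, so there is no stated figure to reproduce.

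**Assumed inputs, not in the article.** IMR before selection is lognormal with median 20 or 25 and log-SD 0.6. The two readings have the same distribution and correlate r on the log scale before selection. There is no drug effect and no time trend. These choices give an enrolled mean of 40 to 43 and SD of 16 to 20. That resembles the 40 and 20 under Sample size, although the article does not say whether those are baseline values.

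**Expected fall.** Let s = 0.6, c = (ln 25 − ln median)/s and K = median × exp(s²/2). Then

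- mean first reading = K × Φ(s − c)/Φ(−c)
- mean second reading = K × Φ(rs − c)/Φ(−c)

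Median 25, r = 0.9: c = 0, K = 25 × exp(0.18) = 29.93, Φ(0) = 0.5.

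- First reading: 29.93 × Φ(0.60)/0.5 = 29.93 × 0.7257/0.5 = 43.44
- Second reading: 29.93 × Φ(0.54)/0.5 = 29.93 × 0.7054/0.5 = 42.23
- Fall: about 1.2 units

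Median 20, r = 0.5: c = 0.372, K = 23.94, Φ(−0.372) = 0.355.

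- First reading: 23.94 × 0.5902/0.355 = 39.8
- Second reading: 23.94 × 0.4713/0.355 = 31.8
- Fall: about 8.0 units

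**Chance of a significant fall.** Simulated with n = 36 and a two-sided paired t-test at 5%, counting falls only (nominal 2.5%). Ranges run over the two medians.

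| r before selection (log scale) | correlation among enrolled (IMR units) | spurious fall (units) | false 'improvement' |
|---|---|---|---|
| 0.98 | about 0.95 | 0.2–0.3 | 4.5–6% |
| 0.95 | about 0.9 | 0.6–0.8 | 7–9% |
| 0.9 | about 0.8 | 1.2–1.6 | 9–15% |
| 0.8 | 0.62–0.66 | 2.5–3.2 | 15–27% |
| 0.5 | 0.30–0.33 | 6.5–8.0 | 38–63% |

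In the same null trials the between-arm t-test on change rejects in about 5% (two-sided) throughout.

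**Other distributions.** Two other lognormal and two normal IMR distributions, with enrolled means of 39 to 48, gave paired-t rates of 22–72% at r = 0.5, 11–34% at r = 0.8, 8–18% at r = 0.9 and 5–11% at r = 0.95. Wilcoxon rates were similar (20–72%, 11–32% and 6–12% at r = 0.5, 0.8 and 0.95). The between-arm error stayed at 4.2–5.5%.

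**The case against.** The strongest reply is that efficacy does not rest on this test. The between-arm comparison comes first in the Analysis section, the sample size is built on a treatment-versus-control contrast, and both arms are re-measured against saline. All of that stands. A reader might infer that the primary comparison is compromised, or that the investigators intend to claim efficacy from the within-arm P-value. The article supports neither: randomisation leaves the between-arm error at about 5%, and no sentence says that the paired result will carry a conclusion.

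A second reply concerns size. A reader might take 63% and 8 units, which equals the article's clinically meaningful difference, as the expected damage. That is the unfavourable corner of undocumented inputs. It needs a correlation of only about 0.3 among enrolled patients, for two readings about 30 minutes apart in one procedure. The article's cut-off of r = 0.8 among enrolled patients matches the 0.9 row, and its highly correlated case lies above that row, where the inflation is smaller. The 8 units are also a between-group quantity, so the comparison gives scale only.

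Third, a fall is not guaranteed: an upward time or procedural trend could offset it. This is accepted. Such a trend would equally prevent the paired test from isolating the drug.

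The reply that a separate analysis plan may settle which tests are descriptive does not remove the point. The article positively specifies the test and gives it no descriptive label.

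**Conclusion.** The paired t/Wilcoxon test as written is not a valid test of salvianolate, because its 'before' value is the reading on which patients were selected. With test-retest noise and no opposing trend, the bias is towards an apparent fall. Its size cannot be fixed from the article. Under the assumptions shown, false 'improvement' runs from about 4.5% at r = 0.98, through 9–15% at r = 0.9, to 38–63% only at r = 0.5, against a nominal 2.5%. The defect is confined to the within-group test and any claim drawn from it. The randomised comparison of the primary end point is sound on this point. The change should be made, but it does not threaten the trial's main result.

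**What to change.** Delete the within-group paired t-test/Wilcoxon hypothesis test. Show mean IMR before and after, and mean change, for both arms side by side as description only. Removing the P-value alone is not enough: a within-arm confidence interval carries the same bias, and a 95% interval that excludes zero is the paired t-test at 5% in another form. Add wording such as: *Because patients were selected on baseline IMR, neither the change within an arm nor its confidence interval is evidence of a drug effect; efficacy conclusions rest only on the randomised between-arm comparison.*

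The cost is one clause deleted and one sentence added. What is lost is a within-arm P-value that has no valid causal reading. Sample size, measurements and the between-arm analysis do not change.

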## Statistical considerations

### Sample size

We use the URL (https://www.cnstat.org/samplesize/5/) to generate the calculated sample size. According to our pre-experimental results, we assume *α* = 0.05, 1-*β* = 0.80, Mean_*t*_ = 20, Mean_*c*_ = 40, *σ* = *S*_*t*_ = *S*_*c*_ = 20, *N*_t_:*N*_c_ = 1:1, and suppose that a 20% IMR reduction (Δ = − 8) is considered of clinically meaningful difference. We get approximately 36 (between 35 and 36) needed patients in each group. Considering the loss rate of 10%, the total sample size will be 78 cases with 39 cases in each group. The equation being used to estimate the sample size is as follows:
$$ n=\frac{2{\left({Z}_{\alpha }+{Z}_{\beta}\right)}^2{\sigma}^2}{{\left({\mathrm{Mean}}_t-{\mathrm{Mean}}_c-\Delta \right)}^2}. $$

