Premature discontinuation of salvianolate, loss to follow-up, and death are possible intercurrent events. As we use treatment policy strategy in our study, we will take a per-protocol analysis, as well as intention-to-treat (ITT) analysis for statistical analysis. Per-protocol analysis includes participants who complete the assigned therapy according to the trial protocol while ITT analysis includes all randomly assigned participants according to the treatment group to which they were originally assigned, regardless of the occurrence of intercurrent events. The ITT analysis will indicate how salvianolate will work in a more real-life setting. If there is evidence that the difference in the treatment depends on certain patient characteristics identified in the baseline assessment, a subgroup analysis will be performed.

The missing data before the intercurrent events will be filled with the measured values of “similar participants.” The similar patients should have the same sex and smoking history (smoker or nonsmoker). Missing values will be imputed by expectation-maximization algorithm through age, systolic blood pressure, diastolic blood pressure, fasting blood glucose, and IMR. Multiple imputation will be used in our study. *P*-value < 0.05 will be considered to indicate statistical significance. All statistical analyses will be performed using the Statistic Package for Social Science (SPSS) software package, version 18.0 (SPSS Inc., Chicago, IL, USA). The results will be published by the chief investigator and major contributors.

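### The primary IMR test is left to be chosen from the data, and the rule dropping ANCOVA when r exceeds 0.8 is wrong in principle, though with equal SDs it costs little precision

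*Protocol article*

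**What the plan says.** All references are to the protocol article.

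- **End points:** "The primary end point will be the IMR change in the immediate phase during the coronary angiography procedure". There is no other primary end point.
- **Statistical considerations, Analysis**, on that end point:
  - "IMR changes between the two groups will be compared by independent" t-test or Mann-Whitney U test. The text gives no criterion for choosing between them.
  - "Analysis of covariance will be used if the baseline and follow-up IMRs are not highly correlated", with the cut-off set at r of 0.8 or less.
  - "If the variables are not normally distributed, they will be transformed into normal distribution by logarithm". It does not say whether this means baseline IMR, 30-minute IMR or their difference, nor whether it comes before or after Mann-Whitney.
- **Same section**, on significance: a P "value < 0.05 will be considered to indicate statistical significance".
- **Implementation and study procedures:** randomization is in blocks, stratified by sex.

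The article gives neither an expected correlation between baseline and 30-minute IMR nor the ratio of their SDs.

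**The concern.** The trial's main conclusion rests on one comparison in 78 patients, yet the text allows several: a mean difference in change, a rank comparison of change, a baseline-adjusted mean difference or, with logs, a ratio. These test different hypotheses and can disagree.

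The one explicit switch depends on a correlation that includes the 30-minute outcome, so the method is settled only after outcomes are known. It also points the wrong way. It implies that a high correlation is a reason to leave ANCOVA for the change score, whereas no correlation makes the change score the more precise of the two. At stake are the credibility of the primary P-value, some precision, and a clear statement of which effect is being estimated.

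**Working it through.** **Inputs.** From Sample size ("According to our pre-experimental results, we assume"): alpha 0.05, power 0.80, means 20 and 40, common SD 20, delta -8, about 36 per group. From Analysis: the cut-off of 0.8. Assumed, because the article does not give them: the correlation r, and k, the ratio of follow-up SD to baseline SD.

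**1. The plan's figure.** n = 2(1.645 + 0.842)² × 20² / (20 - 40 + 8)² = 2 × 6.183 × 400 / 144 = 34.3, so 35 per group, or 36 with the t distribution. This matches the stated figure with one-sided alpha (two-sided gives 43.6). Sidedness is a separate matter; here the figure only supplies n = 36 per arm. The formula contains no r, so it does not show which analysis was intended.

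**2. Precision at any r and k.** In units of the baseline variance:
- change score: 1 + k² - 2rk
- ANCOVA: k²(1 - r²)
- difference: 1 - 2rk + r²k² = (1 - rk)², which is never negative.

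Apart from the one degree of freedom spent on the covariate, ANCOVA is therefore never less precise.

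**3. Size of the loss.** With k = 1 the ratio Var(ANCOVA)/Var(change) is (1 - r²)/(2(1 - r)) = (1 + r)/2.

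| r | k = 1 | k = 0.75 | k = 1.25 |
|---|---|---|---|
| 0.80 | 0.900 | 0.559 | 1.000 |
| 0.85 | 0.925 | 0.543 | 0.991 |
| 0.90 | 0.950 | 0.503 | 0.950 |
| 0.95 | 0.975 | 0.399 | 0.813 |

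Only r above 0.8 counts against the rule, because ANCOVA is kept below that. With equal SDs the loss there is under 10% of variance. Two-sided power for a difference of 8 (SD 20, 36 per arm), change score versus ANCOVA, is 0.873 versus 0.896 at r = 0.85 and 0.967 versus 0.973 at r = 0.90. With k = 0.75 at r = 0.90: 0.5625 × 0.19 / (1.5625 - 1.35) = 0.1069 / 0.2125 = 0.50.

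**4. How stable the switch is.** For an observed r of 0.8 in 72 patients, Fisher's z is 1.099 ± 1.96/√69 = 1.099 ± 0.236, giving a 95% CI for r of 0.70 to 0.87. Near the cut-off the method is partly decided by chance. It can also be moved by the treatment effect. In a simulation with assumed values (lognormal IMR with median 22 and log-SD 0.6, baseline above 25, log-scale correlation 0.9, 35 per arm), pooled r exceeded 0.8 in about 44% of trials with no effect and 31% with a 20% reduction.

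**5. Type I error.** Simulated at 36 per arm, 4,000 replicates, correlations 0.5, 0.8 and 0.9, with lognormal IMR (mean 40, SD 20, baseline above 25) or normal IMR. Simulation standard error is about √(0.05 × 0.95/4000) = 0.3 percentage points.
- r rule followed mechanically, with t-test or Mann-Whitney chosen by Shapiro-Wilk: 4.3% to 5.4%.
- smaller P of t-test and ANCOVA: 6.3% to 7.4%.
- smallest P of all permitted tests, including the log versions for lognormal data: 7.0% to 9.3%.

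The Shapiro-Wilk trigger is an assumption; the article states none.

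**The case against.** The strongest reply is that the r rule does little harm in practice. It keeps ANCOVA exactly where ANCOVA helps most. Selecting patients with IMR above 25 lowers the observed correlation, so the rule would often keep ANCOVA anyway. Under the lognormal assumptions of step 4 with a 20% reduction, it does so in nearly all trials at log-scale correlations 0.6 and 0.8 and in about two thirds at 0.9. Power is then within about 2 percentage points of always using ANCOVA. Followed to the letter, the rule does not inflate type I error. Choice of scale and ordering of tests are also often left to a statistical analysis plan, which is not shown.

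Most of this stands, and it limits the size of the point. It does not remove it: the r condition is a stated rule, not an omitted detail, and it is wrong as stated.

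Three stronger readings are tempting but unsupported.
- **That the plan takes the logarithm of a change score, which fails for negative changes.** The text says only that the variables are transformed. The nearest ones named are baseline and follow-up IMR. Entry requires patients "whose FFR > 0.80 and IMR > 25", and IMR is a positive index, so both can be logged. The fair criticism is that the variable is not identified.
- **That the rule wastes the large gain ANCOVA offers at moderate correlation.** At r of 0.8 or below the plan uses ANCOVA, so that gain is not lost.
- **That data will probably prove non-normal.** Skewed raw IMR does not establish skewed changes or skewed model residuals.

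**Conclusion.** The point holds in a limited form. The article fixes no single primary analysis, makes ANCOVA depend on a correlation that includes the outcome, and leaves the log transformation undefined and in competition with Mann-Whitney. That ANCOVA is never less precise is algebra and needs no assumed value of r or k.

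The sizes do rest on assumptions. The variance loss is under 10% for r above 0.8 with equal SDs, and about half at r = 0.9 if the SD ratio is 0.75. Type I error is near 5% under mechanical use and about 7 to 9% only if the smallest P is reported. Nothing in the article says that will happen, and nothing prevents it. The unfixed choice is a larger problem than the precision lost. This should be corrected before unblinding, but it does not by itself undermine the trial.

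**What to change.** In Statistical considerations, Analysis:

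1. Delete the condition on r.
2. Name one primary analysis before unblinding: ANCOVA of 30-minute IMR on arm, baseline IMR and sex (the stratification factor), used whatever the correlation or normality checks show.
3. State the scale in advance. If it is logarithmic, log both baseline and 30-minute IMR and report the ratio of geometric means with a 95% CI; the 20% reduction in Sample size then corresponds to a ratio of 0.80. If it is the raw scale, report the adjusted mean difference with a 95% CI.
4. Keep the t-test on change and the Mann-Whitney test as sensitivity analyses, labelled as such.

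The cost is a few sentences in an amendment or the analysis plan, with no new data and one degree of freedom for each covariate. On the log scale the small downside is that the headline effect is a percentage, not a difference in IMR units. After unblinding the same change would carry much less weight.

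### The tests named for the four secondary end points make no adjustment for the baseline measurements or for sex, the stratification factor; the tests are valid but give up precision that could be had at no cost

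*Protocol article*

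**What the plan says.** All places are in the protocol article.

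- **End points, for assessment at 7 days:** "the secondary end points will be the total ischemic burden assessed by the Seattle angina scale, quality of life scale, Holter electrocardiography, and 6-min walk" (that is, the walking test).
- **Implementation and study procedures, Table 2:** all four of these measures are marked at screening and at Day 7. The text below the table agrees: "In the screening stage, the investigator conducts a baseline assessment".
- **Same section, on allocation:** "Block randomization stratified by sex will be implemented".
- **Analysis, secondary end points:** the tests are a t-test "or nonparametric tests for continuous variables as well as" a chi-square test, and these "will be used for the secondary end points assessed by the Seattle angina scale, quality of life scale, Holter electrocardiography, and 6-min walk test". No covariate, stratum or baseline term is named. The interval given for a difference in means is the plain two-sample one, on n1 + n2 − 2 degrees of freedom.
- **Analysis, IMR:** "Analysis of covariance will be used if the baseline and follow-up IMRs are not highly correlated". This is the only covariate-adjusted comparison in the article, and it does not name sex.
- **Analysis, missing data:** sex appears again only as a matching variable for filling in missing values.

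**The concern.** Each secondary end point has its own pre-treatment value, which is usually the best single predictor of the value a week later. A plan that measures it and then compares the arms without it leaves explainable variation in the standard error. It also lets chance baseline differences between two small arms affect the estimate. The stratification factor raises a similar issue: stratified blocks force the arms to be balanced on sex, and an analysis that ignores sex does not credit that balance.

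At stake is the article's second aim, the effect on total ischaemic burden. The sample size is justified for IMR alone and no power is stated for these four end points, so their precision depends on the method of analysis.

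**Working it through.** **The only stated figure.** Sample size gives SD 20, means 20 and 40, and Δ = −8, so the working difference is |20 − 40 + 8| = 12. With one-sided α = 0.05 and 80% power, n = 2 × (1.645 + 0.842)² × 20² / 12² = 34.35, rounded up to 35. With the t distribution, power is 0.7996 at 35 per arm and 0.8095 at 36, which matches the stated 35 to 36. This figure concerns IMR only. It is used here solely to supply about 36 evaluable patients per arm.

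**Assumptions (not in the article).** Baseline to Day-7 correlation r = 0.3, 0.5, 0.7; equal variances at the two times; two-sided 0.05. The article says only that a P-"value < 0.05 will be considered to indicate statistical significance", without sidedness.

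**Baseline.** Take the variance of a Day-7 value as 1. A t-test on Day-7 values then has residual variance 1, a t-test on changes 2(1 − r), and analysis of covariance 1 − r². The last divided by the second is (1 + r)/2.

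The effect that an unadjusted Day-7 t-test detects with 80% power at 36 per arm is (1.960 + 0.842) × √(2/36) = 0.66 SD. Power below is at that effect.

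| r | ANCOVA vs Day-7 t-test | ANCOVA vs change t-test | Power, Day-7 | Power, change | Power, ANCOVA | Equivalent n per arm, 36/(1 − r²) |
|---|---|---|---|---|---|---|
| 0.3 | 0.91 | 0.65 | 80% | 65.8% | 83.6% | 39.6 |
| 0.5 | 0.75 | 0.75 | 80% | 80.0% | 89.9% | 48.0 |
| 0.7 | 0.51 | 0.85 | 80% | 95.1% | 97.5% | 70.6 |

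Analysis of covariance is the most precise of the three for any 0 < r < 1. The last column is relative to a Day-7 t-test.

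**Chance imbalance.** Suppose the arms differ at baseline by d. Given that imbalance, the Day-7 comparison is shifted by r × d and the change comparison by (r − 1) × d. Analysis of covariance removes the shift under the linear model.

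**Sex, type I error.** In 20,000 simulated trials with 36 per arm and sex split evenly in each arm, the unadjusted t-test rejected in about 4.5% of null trials when sex explained 6% of the variance, and in about 3.0% when it explained 20%. With sex in the model the rate was about 5% in both. Ignoring sex is therefore conservative.

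**Sex, precision.** Let sex explain a share R² of the variance, and let the sex difference be the same at both times (both assumptions). The within-sex correlation is w = (r − R²)/(1 − R²), and the residual variance with baseline and sex is (1 − R²)(1 − w²). At r = 0.5 and R² = 0.05, w = 0.474 and the residual variance is 0.95 × (1 − 0.224) = 0.737, against 0.750 with baseline alone. The interval narrows by 1 − √(0.737/0.750) = 0.9%. The same sum gives:

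| r | R² = 0.05 | R² = 0.10 |
|---|---|---|
| 0.3 | 1.4% | 3.0% |
| 0.5 | 0.9% | 1.9% |
| 0.7 | 0.5% | 1.0% |

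The gain from sex is thus about 0.5% to 2% of interval width for r of 0.5 to 0.7, and at most 3.0% at r = 0.3.

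**The case against.** Unadjusted tests are valid in a randomised trial. The list of tests is introduced with open wording, and a condensed article may leave the model for each secondary end point to an analysis plan. The text also does not say whether Day-7 values or changes are tested, and a test on changes does use the baseline. The documents nowhere say that sex predicts these outcomes, and the size of any gain rests on correlations they do not give.

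Most of this stands, and it limits the point in four ways.

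- A reader might infer that the baseline is ignored outright. That holds only if Day-7 values are compared.
- A reader might infer a loss equivalent to nearly doubling the trial (1/0.51 = 1.96). That needs r = 0.7 and the Day-7 reading together; at r = 0.3 the figure is 1/0.91 = 1.10. The factor 1 − r² is also a linear-model result and does not carry over directly to rank or chi-square tests.
- A reader might expect 3% to 5% narrower intervals from sex, from √0.95 = 0.975 and √0.90 = 0.949. That ignores what the baseline has already absorbed.
- Logistic regression might seem the natural counterpart for categorical end points. Its conditional odds ratio is a different quantity from the difference in proportions for which the Analysis section plans adjusted Wald intervals, and it suits about 36 patients per arm poorly.

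What does not stand is that this is merely detail left for later. The article names the tests and writes out the unadjusted interval. In the same paragraph it considers analysis of covariance and ties it to IMR. That is a stated choice, and under either reading of the t-test it is not the most precise one available.

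**Conclusion.** The point holds as a free improvement. The tests stated for the four secondary end points are valid but less precise than the collected data allow. For r of 0.3 to 0.7, an assumed range, adjusting for baseline removes 9% to 49% of the residual variance relative to a Day-7 t-test, or 35% to 15% relative to a change-score t-test. Nearly all of the gain comes from the baseline. Sex adds a few per cent of interval width at most, and leaving it out makes the tests slightly conservative.

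The documents do not support reading this as an invalid analysis, an inflated type I error or a flaw in the sample size. The total of 78 was set for IMR and is unaffected.

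**What to change.** - **Continuous secondary end points:** make the main analysis a linear model of the Day-7 value (log-transformed if needed) on arm, that end point's own screening value and sex. Report the adjusted difference with its 95% confidence interval. This also settles whether Day-7 values or changes are analysed.
- **IMR:** include sex in the analysis of covariance.
- **Any categorical secondary end point:** use a Mantel-Haenszel comparison stratified by sex, reported as a difference in proportions.
- **Unadjusted tests:** keep those now listed as sensitivity analyses.

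Cost: wording only. Every variable is already collected, and no visit or patient is added. With 72 evaluable patients the two extra model terms reduce the residual degrees of freedom from 70 to 68. Recruitment began in January 2020, so under the article's Amendments section the revision must go to the ethics committee before it is implemented. It should be fixed before any unblinded data are seen. If an analysis plan already contains these models, only the article's description needs aligning.
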